**3)** **Clinical effect**

The primary and secondary endpoints will be analyzed. Descriptive statistics (mean, standard deviation, median, and minimum and maximum values), 90% confidence interval, and 90% confidence interval of difference in the mean will be calculated.

Primary outcomes

1. Subjective symptom: QOL score (SGRQ)

2. Exercise tolerance: 6-min Walk Test (Walking distance)

Secondary outcomes

1. QOL score (SF-36)

2. MRC dyspnea scale

3. Peak oxygen uptake (Vo2) measured by CPET

4. Food intake

5. Pulmonary function test: VC, FEV1%

6. Respiratory Muscle Strength: MIP, MEP

7. Plasma norepinephrine level

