**9) Target sample size**

Active drug group, 30cases; placebo group, 30 cases; Total cases, 60 cases.

Planned allocation number to each center:

National Hospital Organization Toneyama National Hospital 20 cases

Nara Medical University 16 cases

University of Miyazaki 12 cases

Osaka City University 8 cases

National Cerebral and Cardiovascular Center Research Institute 4 cases

**10)** Expected period of the Clinical trial

From the ethical committee approval in 2005 to June 2008.

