**7)** **Efficacy Assessments**

Efficacy assessments are to be performed before the administration; Weeks 1, 2 and 3 after start of the administration**;** and Week 7 after start of the administration, i.e., 4 weeks after the completion of the administration with double-blind fashion.

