****Before the administration and Week 3 after start of the administration****

1. Subjective symptom: QOL score (SF-36, SGRQ), MRC dyspnea scale
2. Examination: Blood pressure, Heart rate, Auscultation

(c) Body height, Body weight, BMI

(d) Blood test (blood will be collected after resting for 15 minutes)

(e) Peripheral blood examination (including differential leukocyte count)

(f) Biochemical examination (Na, K, Cl, Ca, Mg, GOT, GPT, ALP, LDH, γ-GTP, TP, ALB, T-Bil, D-Bil, T-CHO, H-CHO, TG, Cre, BUN, UA, CK, FBS, HBA1c)

High-sensitive CRP

Hormone (insulin, GH, IGF-1, DHEAS, BNP)

Visceral protein (Prealbumin, Retinol binding protein, Transferrin)

Cytokine (TNF-α, IL-6)

 Peripheral blood test, biochemistry, and DHEAS and visceral protein measurement will be performed at each institution.

 Other samples, i.e., hormones (insulin, GH, IGF-1, and BNP) excluding DHEAS, cytokines (TNF-α and IL-6), and high-sensitivity CRP will be collected to the center and collectively measured.

1. Sympathetic nerve activity (Blood / urinary adrenaline, noradrenalin)

(Plasma and acidic accumulated urine will be used for measurement in blood and urine samples.)

 Samples for sympathetic nerve activity measurement will be collected to the center and collectively measured.

(h) Arterial blood gas analysis (measured in recumbency)

(i) Pulmonary function test (flow volume and spirometric evaluation)

(j) Food intake

Food intake for 3 consecutive days was assessed before ghrelin administration and during the last week of ghrelin therapy. The food intake was averaged for 3 days. Food ingestion will start from 2,000 kcal/day and be increased when the patient eat all.

(k) 6-min Walk Test (walking distance, SpO2, heart rate)

(l) DEXA (Dual-Energy X-ray Absorbitometry); measurement of lean body mass, body mineral content, and fat mass

(m) Electrocardiogram continuously for 24 hours (Holter ECG)

(n) Cardiopulmonary exercise testing (CPET)

Analyzing expired gas, symptom-limited CPET were conducted on an electrically braked cycle ergometer. Peak oxygen uptake and workload were measured. Exercise load will be pedaling for 1 minute at 0 W followed by 5 W/min ramp.

Measurement parameters:  VO2 (VO2max), VCO2, VE (VEmax), VEmax/MVV, VE/VO2, VE/VCO2, HR, BP, O2pulse (VO2/HR), Work rate (WRmax), Borg scale, SpO2

(o) Grip strength

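### The efficacy comparison is stated only as a difference in means, with neither baseline adjustment nor the choice of final value or change named, although baseline SGRQ and 6-min walk distance are scheduled for every patient

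*Protocol*

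**What the plan says.** The efficacy analysis is set out in Section IX, Statistics Analyses, under Clinical effect. For primary and secondary endpoints alike it lists "Descriptive statistics (mean, standard deviation, median, and minimum and maximum values), 90% confidence interval", and then, for the comparison between groups, "90% confidence interval of difference in the mean will be calculated". It names no model, covariate or test, and does not say whether the mean is of the value at the end of treatment or of the change from baseline.

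SGRQ and the 6-min walk test both appear in the Section V list headed "Before the administration and Week 3 after start of the administration". Both appear again in the list for the visit 4 weeks after treatment ends. Each patient is therefore due a baseline, a Week 3 and a Week 7 value of each primary outcome.

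The planned size, in the Summary under Target sample size, is "Active drug group, 30cases; placebo group, 30 cases; Total cases, 60 cases". No effect size, standard deviation or power is given.

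**The concern.** The between-group quantity stands in one sentence with raw summaries (mean, median, extremes), so a statistician following the text could compute a raw difference of final values, a raw difference of changes, or an adjusted difference. These have different precision, and in one data set they can point different ways.

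A final-value comparison carries all of the chance baseline difference that is correlated with outcome. A change score over-corrects for it whenever r is below 1. ANCOVA estimates the correction from the data. In a trial of 60 patients with no stated power calculation, a wider interval than necessary makes a real effect harder to see. The choice between two unadjusted analyses should also not be left open until the key is opened.

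**Working it through.** **Inputs from the protocol.** There are 30 patients per group and the confidence level is 90%. Baseline and Week 3 values of both primary outcomes are scheduled for everyone. The figure of 60 cannot be re-derived, because no effect, SD or power is stated. Only the centre totals can be checked: 20 + 16 + 12 + 8 + 4 = 60.

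**Assumptions.** The SD (σ) is the same at baseline and follow-up and in both groups. The correlation r between baseline and follow-up is not in the protocol, so a range of 0.3 to 0.9 is shown. Results are in units of σ.

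**Variance of the estimated treatment difference, n = 30 per group**

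- Final values: 2σ²/n
- Change scores: (2σ²/n) × 2(1−r)
- ANCOVA on baseline: (2σ²/n) × (1−r²)

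Against final values, ANCOVA therefore saves r². Against change scores the ratio is (1−r²)/[2(1−r)] = (1+r)/2, a saving of (1−r)/2.

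**Half-width of the 90% interval.** For final values it is 1.645 × √(2/30) = 0.425σ (0.432σ with the t quantile on 58 degrees of freedom). The other columns multiply 0.425 by √[2(1−r)] or √(1−r²).

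| r | Final value | Change | ANCOVA | Variance saved vs final | Variance saved vs change |
|---|---|---|---|---|---|
| 0.3 | 0.425 | 0.503 | 0.405 | 9% | 35% |
| 0.5 | 0.425 | 0.425 | 0.368 | 25% | 25% |
| 0.7 | 0.425 | 0.329 | 0.303 | 49% | 15% |
| 0.8 | 0.425 | 0.269 | 0.255 | 64% | 10% |
| 0.9 | 0.425 | 0.190 | 0.185 | 81% | 5% |

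Estimating the baseline slope inflates the ANCOVA variance by roughly 1 + 1/56. At r = 0.5, 0.7 and 0.8 the savings then become about 24%, 48% and 63% against final values, and 24%, 13.5% and 8% against change.

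**Equivalent numbers of patients.** Against final values, 60/(1−r²) gives 80, 118 and 167 at r = 0.5, 0.7 and 0.8. Against change scores, 60 × 2/(1+r) gives 80, 71 and 67.

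**Power for a true difference of 0.5σ** (an illustrative effect, at the two-sided 10% level that matches a 90% interval)

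| r | Final value | Change | ANCOVA |
|---|---|---|---|
| 0.5 | 61.5% | 61.5% | 72.3% |
| 0.7 | 61.5% | 80.4% | 85.7% |
| 0.8 | 61.5% | 92.2% | 94.3% |

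**Why the open choice matters.** The chance baseline difference between groups has an SD of √(2/30) = 0.258σ. At r = 0.8, an imbalance of that size shifts the final-value difference by 0.8 × 0.258 = 0.21σ. It shifts the change difference by (0.8 − 1) × 0.258 = −0.05σ, in the opposite direction. The two unadjusted readings can therefore differ by 0.26σ on the same patients.

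**The case against.** The strongest objection is that the text never says the comparison is unadjusted. A reader might infer that the protocol has fixed a raw comparison of final values, but an ANCOVA estimate is also a difference in means, and nothing excludes covariates. Model form is ordinarily left to a statistical analysis plan, and one may exist. This stands to the extent that the point cannot be put as a wrong estimator already chosen. It does not remove the point: the protocol does state its between-group quantity, and states it so that three different analyses would satisfy it.

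A second objection concerns size. The 64% saving at r = 0.8, equivalent to about 2.8 times the patients (1/0.36), holds only if final values are compared. The protocol speaks of improvement in its objectives and in the rehabilitation section, so change from baseline is at least as plausible, and there the equivalent is 2/(1+r) = 1.11 times. High correlation, which makes the first figure large, makes the second small. This objection stands, so both comparators must be shown.

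Third, a reader might infer that chance imbalance could pass for a drug effect at more than the nominal rate. It does not: under randomisation the unadjusted difference is unbiased, and its interval already allows for such imbalance. What is lost is precision.

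Fourth, a reader might infer that centre must be in the model because patients are planned by centre. The protocol states no stratification by centre and gives no between-centre variance. Two planned centres have only 8 and 4 patients. No benefit from a centre term can be shown.

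**Conclusion.** The point holds as an incompletely stated and improvable estimator, not as a biased or invalid one. Naming the baseline-adjusted difference would reduce the variance by 25% to 64% against final values, or by 25% down to 10% against change scores, for r from 0.5 to 0.8. The slope costs one to two percentage points of this. Over the range of r shown, ANCOVA is the more precise under either reading, and it removes the choice between two analyses that can disagree.

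The size rests on an assumed r and on equal variances at the two times. The protocol gives neither, so no single figure can be claimed.

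**What to change.** In Section IX, Clinical effect, define the treatment effect for SGRQ and 6-min walk distance as the adjusted mean difference, with its confidence interval, from an ANCOVA of the Week 3 value on treatment and the baseline value of the same variable. Apply the same definition to the continuous secondary outcomes that have a baseline value. Use the same model at Week 7 for outcomes measured then; CPET, food intake and plasma norepinephrine are not in that visit's list. Count weeks from the start of administration, because the schedule table numbers the same visits Week 4 and Week 8. Keep the unadjusted means as description.

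The change needs a sentence or two and no new data. It uses one residual degree of freedom (58 to 57). Adding centre is optional; five centres would take four more, and the gain above does not depend on it. The definition should be in place before the key is opened for analysis.

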**X Audit of the clinical trial**

A person approved by the Ethics Committee will audit the clinical trial.

**XI Payment and compensation for health damage**

**1)** **Payment for study-related expenses**

Costs for the test drug and tests other than health care services provided by national health insurance will be covered by the Grant for Health Science.

1. **Compensation for health damage**

When health damage occurs in a subject due to the clinical trial, the subject can rapidly receive appropriate treatment. Compensation for this health damage is limited to treatment only.

**XII Intellectual property**

When a patent and economic profit related to the patent are produced as a result of the clinical study, the right belongs to the collaborative research institutions and persons executing the study including the country, research institutions including private companies, and researchers executing the study.

**XIII Items related to the Act on the Protection of Personal Information Held by Administrative Organs**

Personal information will be managed following the Act on the Protection of Personal Information Held by Administrative Organs.

1) Items of accumulated and analytical data are specified as those presented in Attachment 1 (case report form). These are the minimum necessary data for the study.

2) Data will be stored in 2 personal computers exclusive for management not connected to the hospital LAN. Each trial collaborator will use a single copy of case report form, and filled case reports will be strictly kept in custody with lock. Case reports which became unnecessary will be shredded thorough a shredder and discarded.

3) The personal computers for data management will be managed using devices to protect from robbery, such as wire lock. The system will be managed by access control and user authentication.

4) Samples collected from subjects will be immediately made anonymous by labeling with patient numbers.

5) When a change in the purpose of the use of private information presented at the time of collecting the information is judged as exceeding the rationale range, re-agreement will be obtained.

Information of the patients will be handled using only anonymous patient identification numbers. The concrete management method is as follows: When a target patient is registered as a subject of this clinical study, the patient will be recorded in the collation table after assigning a patient identification number. This table will be strictly managed by the personal information controller. The table of patients at NCVC will be strictly managed by [name], Director, Department of Radiology and Nuclear Medicine, NCVC, and those of patients at the other institutions by responsible persons of the individual institutions. Case reports labeled with identification numbers alone will be collectively managed strictly by [name], Director, Department of Regenerative Medicine & Tissue Engineering, NCVC. The risk of personal information leak is markedly reduced by separately and strictly keeping the table and case reports.

